### ***PET Image Reconstruction and Analysis Procedures***

The data obtained during the various PET acquisitions will be reconstructed to produce time-based 3D image series. Only reconstruction algorithms approved for use with the device (operation software approved by Health Canada during the scanner's approval process) will be used. PET images will be processed and analyzed using PMOD imaging software with a voxel-based and region-specific analysis method validated by [name] laboratory.

For brain imaging data, a correction for multiple comparisons will be applied (false discovery rate correction).

### ***MRI Image Analysis***

MRI acquisitions conducted during the two visits include various modalities to measure, among other things, cerebral perfusion, brain activity, brain volumes, and the integrity of white matter tracts. Image processing and analyses will be conducted in collaboration with collaborator [name].

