### 6.3 Summary of the study

| Table 1. Summary of study procedure                      | min | Eligibility | PRE        | TEP pre    | POST        | TEP post    |
|----------------------------------------------------------|-----|-------------|------------|------------|-------------|-------------|
| Weeks since admission to clinique PEP             |     | 0-1  | 0-1 | 0-1 | 6-10 | 6-10 |
| Consent                                                  | 15  | X           |            |            |             |             |
| Blood test                                               | 5   |             | x          |            | x           |             |
| Physical measure                                         | 10  |             | X          |            | X           |             |
| MRI eligibility questionnaire                            | 2   | X           |            | X          |             | X           |
| Prenancy test                                            | 2   | x           |            | X          |             | X           |
| DUP                                                      | 2   | X           | X          |            |             |             |
| Brief Psychiatric Rating Scale (BPRS)             | 15  |             | X          |            | X           |             |
| Clinical Global Impression, Severity (CGI-S)      | 5   |             | X          |            | X           |             |
| Calgary Depression Scale for Schizophrenia (CDSS) | 10  |             | X          |            | X           |             |
| Global Assessment of Functioning (GAF)            | 2   |             | X          |            | X           |             |
| Brief Assessment of Cognition (BACS)              | 30  |             | X          |            | X           |             |
| Side Effect Rating Scale (UKU)                    | 20  |             | X          |            | X           |             |
| Alcohol Use Disorders Identification Test (AUDIT) | 2   |             | X          |            | X           |             |
| Drug Disorders Identification Test (DUDIT Drug)   | 2   |             | X          |            | X           |             |
| Fagerström Test for Nicotine Dependence (FTND)    | 2   |             | X          |            | X           |             |

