| Sleepiness Scale (ESS)                            | 1   |             | X          |            | X           |             |
| Simple Physical Activity-questionnaire (SIMPAQ)   | 5   |             | X          |            | X           |             |
| Barnes akathisia scale (BAS)                      | 2   |             |            | X          |             | X           |
| Food Craving questionnaire (FCQ)                  | 5   |             |            | X          |             | X           |
| Medication list (type + dose)                     | 2   | X           |            |            | X           |             |

|                                       |     |  |  |   |   |   |
|---------------------------------------|-----|--|--|---|---|---|
| Adherence questionnaire (MARS) | 2   |  |  |   | X |   |
| PET scan                              | 120 |  |  | X |   | X |
| MRI                                   | 30  |  |  | X |   |   |
| Continuous glucose monitoring         | 15  |  |  | X |   | X |

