### V2 and V4 Imaging Visits (BEFORE and AFTER)

---

Location: Centre for Molecular Imaging of Sherbrooke (CHUS Fleurimont)

Duration: 3 hours (fasting for 4 hours before)

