#### Procedure:

- Reconfirm consent.
- Verification of MRI contraindication questionnaire.
- Pregnancy Test
- 15 minutes MRI Scan (volumetric and vascular system imaging).
- Two intravenous catheters will be installed in the forearms, and blood glucose will be measured.
- 20 minutes PET Scan with 11C-Acetoacetate with blood sampling.
- Break: 40 minutes break.
- 30 minutes PET Scan with 18F-FDG with blood sampling.
- Snack provided after the imaging session.

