#### Procedure:

- The participant will lie on their back on a bed that moves into the MRI machine (MRI3T Ingenia Philips).
- The imaging session will take about 10 minutes (plus installation time), during which the participant must avoid moving their head.
- The MRI machine and head coil used in this study are approved by Health Canada and are routinely used at the CHUS Research Center.
- The participant will be monitored throughout the imaging session, and verbal communication will be possible at all times during the exam.

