**Secondary variables related to structural changes measured by MRI:**

- Global and regional brain volumes (ml);
- Cortical thickness (mm);
- Structural changes in brain vasculature (score).

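### Table 1 schedules the MRI at the BEFORE imaging visit only, while sections 6.4 and 8.1 place it at both visits, and section 8.1 names MRI measures that are neither in the scan description nor in the variable list

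*Protocol*

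**What the plan says.** Four parts of the protocol describe the MRI.

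- **Section 6.3, Table 1.** The columns run "Eligibility | PRE | TEP pre | POST | TEP post". The MRI row gives 30 minutes and has one mark, under TEP pre; the TEP post cell is empty. The row above it is marked at both imaging visits: "PET scan | 120 | | | X | | X". The MRI safety screen is also repeated at the last visit: "MRI eligibility questionnaire | 2 | X | | X | | X".
- **Section 6.4.** One procedure list, headed "V2 and V4 Imaging Visits (BEFORE and AFTER"), includes "15 minutes MRI Scan (volumetric and vascular system imaging").
- **Section 6.6, MRI Imaging.** "The imaging session will take about 10 minutes (plus installation time").
- **Section 8.1, the paragraph on analysing the MRI.** It reads: "MRI acquisitions conducted during the two visits include various modalities to measure, among other things, cerebral perfusion, brain activity, brain volumes, and the integrity"; this last item refers to the white-matter tracts.

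Section 8.2 then lists, under "Secondary variables related to structural changes measured by MRI", brain volumes, cortical thickness and a score for change in the brain vasculature. Section 8.1 assigns BEFORE versus AFTER comparisons to a paired Wilcoxon signed-rank test. In section 4, brain structure by MRI appears under the exploratory objectives and in neither secondary objective.

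**The concern.** A change in volume, cortical thickness or vasculature needs a scan at both time points. The schedule table is what staff commonly use to book visits, and section 6.5 allows the PET and the MRI to be split into separate appointments. An empty MRI cell at the last imaging visit could therefore simply be followed. Each participant is in the study for only 5 to 7 weeks (section 6.1), so an AFTER scan that was never booked cannot be recovered.

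A second, separate mismatch concerns content. Section 8.1 describes a broader set of MRI measures than section 6.4 acquires or section 8.2 lists, so the protocol gives two accounts of which images are collected. The tier label for the MRI variables also differs between sections 4 and 8.2.

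**Working it through.** No sample size, power or significance figure is at issue. The check sets the passages side by side and counts.

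**1. Is the empty cell a reading error?** The table was read from a PDF, so a lost mark cannot be fully excluded. The PET and glucose-monitoring rows in the same part of the table keep both marks, so a column shift is unlikely.

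**2. MRI scans per completer and resulting pairs.** Section 5.1 plans for 10 completers.

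| Source followed | MRI scans per completer | BEFORE/AFTER pairs |
|---|---|---|
| Table 1 (section 6.3) | 1 | 10 × 0 = 0 |
| Sections 6.4 and 8.1 | 2 | up to 10 × 1 = 10 |

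With 0 pairs the signed-rank test cannot be run for any of the three MRI variables. With up to 10 pairs it can be run for all three.

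**3. Measures named in section 8.1 against the scan in 6.4 and the list in 8.2.**

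| Measure in 8.1 | Named in 6.4? | Variable in 8.2? |
|---|---|---|
| Brain volumes | Yes | Yes |
| Perfusion | Unclear: vascular imaging is not defined | No |
| Brain activity | No | No |
| White-matter integrity | No | No |

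Two of the four measures have no stated acquisition, or three if vascular imaging excludes perfusion. In the other direction, all three variables in 8.2 fit the volumetric and vascular scan of 6.4. The content mismatch therefore takes nothing away from the listed variables.

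**4. Scan time.** The figures are 30 minutes (Table 1), 15 minutes (6.4) and about 10 minutes plus installation (6.6). Table 1 may give slot times: its PET entry is 120 minutes, while the steps in 6.4 sum to 20 + 40 + 30 = 90. On that reading the 30 minutes can include set-up, and what remains is 10 against 15 minutes of scanning.

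**5. Would an MRI fit into V4?** The times marked in Table 1 under TEP post are PET 120, glucose monitor 15, MRI questionnaire 2, pregnancy test 2, akathisia scale 2 and food-craving questionnaire 5: 120 + 15 + 2 + 2 + 2 + 5 = 146 minutes. Adding 30 for the MRI gives 176, within the 3 hours (180 minutes) that section 6.4 allots.

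**The case against.** The best defence is that one empty cell stands against several passages. Section 6.4 lists the scan for both visits, section 8.1 says two visits, section 8.2 speaks of changes, and Table 1 itself repeats the MRI safety questionnaire at the last imaging visit. The intention to scan twice is fairly clear, and nothing says that Table 1 overrides the text. This stands, and it limits the point to a contradiction with a conditional consequence.

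Several stronger readings are tempting, and the documents do not support them:

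- *That the MRI change variables cannot be derived.* This is true only if Table 1 governs; under section 6.4 they can be.
- *That the missing modalities undermine the listed variables.* They do not, as the comparison with section 8.2 shows.
- *That the short scan proves the extra measures are not acquired.* No sequence list is given, so the duration settles nothing.
- *That the AFTER PET regions would have to be drawn on the BEFORE MRI, which would reach the primary variables.* Section 8.1 describes a voxel-based and region-specific PET method but does not say that regions are drawn on the MRI.

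The difference in tier label also has no demonstrated effect on the analysis. Section 8.1 sets one significance threshold and applies a false discovery rate correction to brain imaging data, without a hierarchy by tier. It is a labelling fault.

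**Conclusion.** The contradiction is real and should be fixed. Table 1 provides for one MRI per participant; sections 6.4 and 8.1 provide for two. The consequence depends on which is followed: 0 pairs among 10 planned completers under Table 1, up to 10 under section 6.4. For all three MRI variables in section 8.2, that decides whether the planned paired comparison exists.

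The mismatch in measures is a lesser fault. Two, arguably three, of the four measures in section 8.1 have no stated acquisition, and those same three have no listed variable. The variables that are listed are unaffected.

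The conclusion assumes that the MRI row of Table 1 was read correctly and that 10 participants complete. It concerns non-primary variables in a pilot study, and no effect on the primary PET variables is shown. It therefore ranks below the faults that must be corrected before the study can proceed, although a missed AFTER scan would be a permanent loss.

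**What to change.** Confirm whether an MRI is done at V4, then make the passages agree.

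- **If it is done:** mark the MRI under TEP post in Table 1.
- **If only one MRI is intended:** remove the AFTER MRI from sections 6.4 and 8.1, and the MRI change variables from section 8.2.
- **Measures:** limit the MRI paragraph of section 8.1 to the volumetric and vascular measures in 6.4 and 8.2, or list the additional sequences in 6.4 if they are really acquired.
- **Scan time:** use one figure in Table 1, 6.4 and 6.6, and say whether it includes installation.
- **Tier:** give the MRI variables the same label in sections 4 and 8.2.

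The cost is one table cell and some wording. If the V4 scan is confirmed, nothing is added beyond what section 6.4 already describes, and by the table's own times it fits the visit. If staff have been working from Table 1 alone, the correction does mean one more MRI per participant in practice, so it should be settled before participants reach V4.

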## **8.2 List of variables**

---

Study variables will be collected by trained and delegated team members using the instruments cited in the protocol or based on laboratory and imaging analyses. Depending on the type of variable (clinical, imaging, etc.), appropriate training will be provided and documented according to SOPs and GCP guidelines by the team physician or expert collaborators. Wherever possible, evaluations for the same participant will be conducted by the same evaluator.

Certain source data (e.g., medication lists, CHUS analysis results, etc.) will be extracted from the electronic medical record system Ariane, but only for data and time points specified in the protocol. Other source data will come from scores obtained from the instruments, laboratory analyses, or imaging analyses.

Data will be entered into a computerized database (Excel file or REDCap depending on the type of data). The procedure will be detailed in the study manual, along with data entry and verification/validation procedures.

### ***Primary variables related to changes in cerebral energy metabolism:***

- Cerebral metabolic rate of glucose ( $\mu\text{mol}/100 \text{ g}/\text{min}$ ) quantified with 18F-FDG;
- Net glucose influx with 18F-FDG ( $\text{Kglu}; \text{min}^{-1}$ );
- Cerebral metabolic rate of acetoacetate with 11C-AcAc ( $\mu\text{mol}/100 \text{ g}/\text{min}$ );

- Net acetoacetate influx with 18F-FDG (Kglu; min).

**Secondary variables related to clinical improvement:**

- % change in the Brief Psychiatric Rating Scale (raw score after/raw score before\*100).

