### Secondary Objectives

---

- 1) In patients with a first episode of psychosis, compare the effect of 4 to 6 weeks of antipsychotic medication on brain metabolism measured by PET scan (cerebral uptake of 11C-Acetoacetate + 18 Fluorodeoxyglucose) to clinical improvement (measured by the percentage change in the Brief Psychiatric Rating Scale) and systemic metabolism (measured by continuous glucose monitoring).
- 2) Compare brain fuel utilization measured by PET scan (cerebral uptake of 11C-Acetoacetate + 18 Fluorodeoxyglucose) between AP-naïve patients with a first episode of psychosis and an existing dataset of healthy controls (matched for age and sex).

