### **8.1 Analyses**

All data will be compiled, and differences BEFORE vs. AFTER for the various measurement variables will be assessed using Wilcoxon signed-rank non-parametric tests for paired data.

Correlations will also be performed, particularly between brain function (variables related to global and regional changes in cerebral energy metabolism), blood levels of various measured parameters, and scores from clinical questionnaires (global psychopathology, functioning, depression, cognition, etc.).

In a second phase, comparisons will be made with a control group from a brain imaging database conducted in age-matched participants without the condition (Project 08-111 [name]).

The significance threshold will be set at  $p < 0.05$ . All statistical analyses will be performed using SPSS 24.0 software (SPSS Inc, Chicago, USA).

As this clinical study includes an exploratory component, new analyses or complementary analyses may be added based on the literature or preliminary analyses.

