**Exploratory variables related to psychopathology and clinical status:**

- DUP;
- Medication lists and dose equivalence;
- Raw scores for various clinical questionnaires:
  - Clinical evaluation and symptoms: BPRS, CGI-S, ESS, BAS;
  - Depression: CDSS;
  - Functioning: GAF;
  - Cognition: BACS;
  - Medication: UKU, MARS;
  - Alcohol and drug consumption: AUDIT, DUDIT, FTND;
  - Physical activity: SIMPAQ.

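### The secondary variable labelled as percentage change in BPRS is defined as the follow-up score as a percentage of baseline, so every value is 100 points above the change it is meant to report

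*Protocol*

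**What the plan says.** Secondary objective 1 (Protocol section 4) relates the effect of antipsychotic treatment on brain metabolism to "clinical improvement (measured by the percentage change in the Brief Psychiatric Rating Scale"). It gives no formula.

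The formula is in section 8.2. Under the heading "Secondary variables related to clinical improvement" there is a single entry: the % "change in the Brief Psychiatric Rating Scale (raw score after/raw score before", then multiplied by 100 and the bracket closed. No other part of the protocol changes this formula or defines the percentage change differently.

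Three other places bear on how the variable is used:

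- Table 1 (section 6.3) schedules the BPRS at the PRE and POST clinical visits, so both scores needed are collected.
- Section 8.1 says that BEFORE/AFTER differences "will be assessed using Wilcoxon signed-rank non-parametric tests for paired data". It also plans correlations between brain metabolism variables and "scores from clinical questionnaires (global psychopathology, functioning, depression, cognition, etc".), with significance at p < 0.05.
- Section 8.2 lists the raw BPRS score separately among the exploratory variables ("Clinical evaluation and symptoms: BPRS, CGI-S, ESS, BAS").

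**The concern.** The label and the formula in the same line describe different quantities. A percentage change is zero when nothing changes. The ratio given is 100 when nothing changes. One of the two has to give way, and the objective in section 4 points to the label.

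This is not a detail left for a later analysis plan. The protocol states an explicit formula, and a data-entry sheet or analysis plan that follows it would carry the error forward.

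At stake is the description of clinical improvement in a named secondary objective. A patient whose score fell by 32% would be tabulated with a change of 68%, and a patient who did not change at all with a change of 100%. Section 5.1 says that the pilot is meant to supply preliminary data to secure funding for future studies, so a misread summary could enter later planning. The variable also stands under a heading about improvement while no sign convention is given.

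**Working it through.** **Inputs**

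- Formula as stated (section 8.2): R = 100 × after/before.
- Percentage change, as named in section 4 and in the label in section 8.2: C = 100 × (after - before)/before.
- The protocol gives no BPRS values. The scores below are illustrative.
- Assumption: a higher BPRS score means more severe symptoms. The protocol does not state the direction.

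**Step 1. Relation between the two quantities**

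C = 100 × after/before - 100 = R - 100, so R = C + 100 for every patient, whatever the baseline.

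**Step 2. Illustrative values**

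| Before → after | R, as the protocol defines it | C, percentage change |
|---|---|---|
| 50 → 50 | 100 | 0 |
| 50 → 40 | 80 | -20 |
| 50 → 34 | 68 | -32 |
| 50 → 25 | 50 | -50 |
| 50 → 60 | 120 | +20 |

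**Step 3. Could another reading of the formula rescue it?**

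If the multiplication is taken first, the result is after/(before × 100). For 50 → 50 this is 50/5000 = 0.01. That is not a percentage change either.

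**Step 4. Effect on the planned analyses**

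- *Correlations.* Adding a constant to a variable leaves both Pearson and Spearman coefficients unchanged. A simulated set of 10 patients confirmed it: Spearman 0.030 with R and with C, Pearson 0.185 with R and with C. The sign reverses (to -0.030 and -0.185) only if the variable is re-expressed as percentage reduction, 100 × (before - after)/before = 100 - R.
- *Paired Wilcoxon test.* It compares BEFORE and AFTER measurements. The raw BPRS score is listed separately, so this test does not need R.
- *Test of the variable against zero.* The protocol does not plan one. If someone ran it on R with 10 patients, all ten values would be positive, and the exact two-sided signed-rank p-value would be 2/2^10 = 0.002 whether or not anyone had changed.

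**Step 5. Conditional point on the scale minimum**

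The protocol states neither the BPRS version nor how items are anchored. If items are scored from 1, the lowest possible total is above zero: 18 for 18 items, 24 for 24 items (both assumptions). The corrected change is then 100 × (after - before)/(before - minimum).

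| Before → after | Minimum 0 | Minimum 18 | Minimum 24 |
|---|---|---|---|
| 50 → 34 | -16/50 = -32% | -16/32 = -50% | -16/26 = -61.5% |
| 60 → 42 | -18/60 = -30% | -18/42 = -42.9% | -18/36 = -50% |
| 40 → 30 | -10/40 = -25% | -10/22 = -45.5% | -10/16 = -62.5% |

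With a minimum of 0, the patient going from 60 to 42 improves more than the one going from 40 to 30. With a minimum of 18 or 24 the order reverses. If items are scored from 0, the correction disappears.

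**The case against.** The best defence is that little of the planned inference depends on this. R and C differ by a constant, so no correlation changes in size, sign or p-value. The paired test can use the raw scores. The sample size in section 5.1 does not rest on the BPRS, and the study is an observational pilot aiming for 10 completers. The formula is also printed beside the label, so a careful reader can see what was computed. All of this stands, and it limits the severity. It does not make the definition right, because a table headed percentage change would still carry values 100 too high.

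A reader might infer more: that the direction is wrong and that every correlation with improvement changes sign. The documents do not support that. Both sections speak of percentage change, and for a signed change a lower value means a lower follow-up score, exactly as for the ratio. The sign would flip only if the variable were read as percentage reduction, which neither section says. The real gap is that no direction is stated.

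A reader might also infer that the raw-score ratio certainly misorders patients. That depends on a BPRS version and item anchoring that the protocol does not give and that a study manual or analysis plan may fix. It is a reason to state the version, not an established error.

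**Conclusion.** The definition in section 8.2 is wrong for the quantity that it names. Every value is exactly 100 above the percentage change called for in secondary objective 1: 100 instead of 0 for no change, 68 instead of -32 for 50 to 34. This follows from the formula alone and needs no assumption about the scale.

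The consequence is confined to the reported level of clinical improvement and its interpretation. The planned correlation tests give the same results as they would with a signed percentage change, and the paired Wilcoxon tests on raw scores are untouched.

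Reading lower values as improvement assumes that higher BPRS scores are more severe. The understatement of improvement and the change in patient order hold only if items are scored from 1. Severity: minor to moderate.

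**What to change.** - In section 8.2, define the variable as 100 × (after - before)/before and state that negative values mean improvement, with the scoring direction of the BPRS given.
- Make the wording in section 4 (secondary objective 1) and section 8.2 agree. If the ratio is what is really wanted, rename it as the follow-up BPRS score as a percentage of baseline in both places.
- State the BPRS version and item anchoring. If items are scored from 1, use 100 × (after - before)/(before - scale minimum). If they are scored from 0, no correction is needed.

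The cost is one line of protocol wording, plus the matching formula in the database or analysis plan. No new data, visits or patients are needed, since both BPRS scores are already scheduled.
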